### Interim analyses {21b}

Interim analyses will not be necessary due to the preceding telephone screening (T0). The study will be terminated once 84 participants have been completely tested.

### Methods for additional analyses (e.g., subgroup analyses) {20b}

Subgroup analyses for age, sex, and school type are planned. The analyses of the relaxation reactions will be adjusted for the TSST condition if there will be differences in the stress responses between the TSST-IV and the TSST-VR.

### Methods in analysis to handle protocol non-adherence and any statistical methods to handle missing data {20c}

If data is missing, a distinction will be made between data missing at random and missing not at random by computing a Missing Completely At Random (MCAR) test. For data missing at random (e.g., contaminated saliva samples), multiple imputation and maximum likelihood estimation can be used [55]. Completely missing data (e.g., due to failure of technical components) will be excluded. The handling of missing data in questionnaires will depend on the recommendations in the respective manual. Outliers (e.g., due non-adherence) will also be analyzed and excluded if necessary.

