### Sample size {14}

To estimate the needed sample size, an a priori power calculation was carried out using G*Power [26]. Based on the medium average effect size of a recent meta-analysis of Helminen, Morton, Wang, and Felver [7], an effect size of *f* = .30 was expected. Therefore, a sample size of 84 persons was determined to achieve a power of 95%. Thus, the currently planned study aims at a sample size of *N* = 84. The allocation of participants to the groups will be randomized.

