## Statistical methods

### Statistical methods for primary and secondary outcomes {20a}

The parameters of the objective stress reactions will include heart rate, gaze behavior, cortisol, and alpha-amylase. For the analysis of the subjective stress reactions, we will use the self-reported mood ratings of the participants. The saliva samples will be determined by an external laboratory to analyze cortisol and alpha-amylase responses. For statistical analysis, we will use the software IBM SPSS Statistics 28 (IBM Corp., Armonk, NY) and R [52]. After checking the normal distribution of the data, parametric or non-parametric tests will be applied accordingly. Possible differences in the responses of cortisol, alpha-amylase, heart rate, gaze behavior, and mood ratings between the groups (between-subject factors: TSST-VR vs. TSST-IV, HCE vs. NR) and over time (inter-subject factor) will be investigated by means of (repeated measures) analyses of variance ((rm)ANOVAs, parametric) or Mann-Whitney *U* tests / Friedman tests (non-parametric), and post hoc *t*-tests. Equivalence tests will also be used to investigate a comparable increase in the stress responses between the TSST conditions. For this purpose, mean or median values will be calculated from the variables for each group, depending on the distribution of the data and the test used. Area under the curve (AUC) values will also be calculated for analysis of changes in hormonal stress responses [53]. Possible associations between subjective sleep quality / quantity, mood, personality traits and hormonal awakening responses, diurnal profiles, and stress reactions will be analyzed by means of correlations and regression analyses. Again, parametric (e g., Pearson correlation) or non-parametric tests (Spearman or Kendall correlation) will be used depending on the normal distribution and scale level of the data. For multiple comparisons, the *p* values will be corrected according to the false discovery rate (FDR) [54]. Here, the primary outcome variables are corrected collectively across all parameters due to the underlying common hypothesis of a multimodal stress response to the TSST. The statistical significance level will be set to *α* = .05.

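### The missing-data rule relies on an MCAR test to tell MAR from MNAR, which that test cannot do, and no handling is stated for data judged MNAR

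*Protocol article*

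**What the plan says.** The protocol article, section {20c} on non-adherence and missing data, sets out four steps.

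- Classification: "a distinction will be made between data missing at random and missing not at random by computing a Missing Completely At Random (MCAR) test".
- Handling of one class: "For data missing at random (e.g., contaminated saliva samples), multiple imputation and maximum likelihood estimation can be used".
- Exclusion of a separately named category: "Completely missing data (e.g., due to failure of technical components) will be excluded".
- Questionnaires: "The handling of missing data in questionnaires will depend on the recommendations in the respective manual".

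The section gives no handling for data judged missing not at random, and no sensitivity analysis for that case. Section {20a} says that group and time differences in the primary outcomes "will be investigated by means of (repeated measures) analyses of variance" or by non-parametric tests. Nothing elsewhere in the article corrects the description of the MCAR test.

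**The concern.** The test is given a task it cannot perform. An MCAR test sets missing completely at random against departures that show in the observed data. MAR and MNAR both depart from MCAR. What separates them is whether missingness still depends on the unobserved values once the observed ones are taken into account, and no test on the observed data can see that.

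The label matters because the next sentence ties imputation and likelihood methods to the missing-at-random class. Whether they are used therefore rests on a pre-test that cannot identify the class, and is settled after the data have been seen.

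The equivalence question between TSST-VR and TSST-IV is the most exposed. Section {22} foresees VR sickness, which can arise only in the VR arm, and stopping because the stress is unbearable, which is close to the outcome being measured. Losses of either kind may be informative and may differ by arm.

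**Working it through.** **1. What the test can see.** Let R be the missingness indicator, Yobs the observed values and Ymis the unobserved values.

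- MCAR: P(R | Yobs, Ymis) = P(R)
- MAR: P(R | Yobs, Ymis) = P(R | Yobs)
- MNAR: P(R | Yobs, Ymis) still depends on Ymis

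Little's statistic is d² = Σj nj (ȳj − μ̂j)ᵀ Σ̂j⁻¹ (ȳj − μ̂j), summed over missingness patterns j and using only the variables observed in each pattern. It is a function of R and Yobs alone. Dependence on Ymis reaches it only through the correlation of Ymis with Yobs.

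**2. Inputs from the article.** N = 84 (section {14}) and a level of .05 (section {20a}: "The statistical significance level will be set to *α* = .05").

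**3. The plan's own figure.** Section {14} states that "an effect size of *f* = .30 was expected" and that "a sample size of 84 persons was determined to achieve a power of 95" per cent. For a between-groups effect in a repeated-measures ANOVA, λ = N f² m / (1 + (m − 1)ρ). With two groups, m = 8 (the saliva samples at T2) and ρ = 0.5 (an assumption; the article gives none), λ = 84 × 0.09 × 8 / (1 + 7 × 0.5) = 60.48 / 4.5 = 13.44. The smallest N reaching 95% power is 84, so the figure reproduces. It serves below only as the simulated sample size; the point does not depend on it.

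**4. Simulation of the test.** All settings here are assumptions, because the article gives no missing-data rate or mechanism. Two standard normal variables, the first complete and the second partly missing. Missingness is logistic, with probability 20% at the mean and slope 1 on nothing (MCAR), on the observed variable (MAR) or on the missing variable itself (MNAR). There are two patterns, so df = (2 + 1) − 2 = 1. Each cell has 3000 runs, giving a Monte Carlo standard error of at most √(0.25/3000) = 0.009.

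| Mechanism (correlation) | Rejected, N = 84 | Rejected, N = 1000 |
|---|---|---|
| MCAR (0.5) | 5.3% | 4.8% |
| MAR (0.5) | 92.9% | 100% |
| MNAR (0) | 4.8% | 5.1% |
| MNAR (0.3) | 17.3% | 94.1% |
| MNAR (0.5) | 37.6% | 100% |
| MNAR (0.9) | 87.5% | 100% |

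**5. From test result to label.** The article does not say which result gives which label. The natural reading is that a significant result means not at random. At N = 84, MAR data would then be labelled not at random in 92.9% of runs. MNAR data would be labelled at random in 100 − 4.8 = 95.2%, 100 − 17.3 = 82.7%, 100 − 37.6 = 62.4% and 100 − 87.5 = 12.5% of runs as the correlation rises. The reverse reading also fails: MCAR data would be labelled not at random in 100 − 5.3 = 94.7% of runs, and strongly correlated MNAR data would be labelled at random in 87.5%.

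**6. Is it a sample-size problem?** No. At N = 1000 the test rejects in every MAR run and in every MNAR run with correlation 0.5 or 0.9, while MNAR with correlation 0 still looks like MCAR.

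**The case against.** The strongest defence is that the wording is loose and the intention sound: at random may stand for MCAR, and not at random for any systematic loss. The test would then do what is claimed. But imputation and likelihood methods would be attached to MCAR data, where bias is least at issue, and MAR data, for which they are designed, would have no stated handling. The rule still fails.

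Other points limit the concern, and they stand.

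- A reader might infer that data labelled not at random are then excluded. The text does not say so. Exclusion is tied to completely missing data, illustrated by technical failure and so by cause. If that phrase was meant as MCAR, exclusion would depend on the test, but the article does not say this.
- A reader might also infer that repeated-measures ANOVA will drop every participant with one lost saliva sample. Section {20c} names contaminated saliva samples as data for which imputation or likelihood methods can be used, so complete-case loss of single samples is not the stated plan. The wording is permissive, however, and does not commit to those methods.
- Losses from VR sickness or distress are partly governed by a separate rule in section {22}. Sickness scores (VR arm only), mood ratings and adverse-effect notes are recorded, so missingness driven by them could plausibly be MAR given those variables. That supports arguing MAR from recorded reasons rather than from a test.
- Section {21b} ends the study once 84 participants have been completely tested, which may mean that losses are replaced. Replacement restores numbers but does not remove bias from selective loss.
- A condensed article may leave the covariance structure and the form of a sensitivity analysis to an analysis plan. That explains missing detail, but not a rule stated wrongly.

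**Conclusion.** The point holds as a should-fix. Section {20c} assigns to an MCAR test a distinction that it cannot make at any sample size, lets the use of imputation or likelihood methods rest on the resulting label, and states nothing for data judged MNAR. This follows from the definitions. The simulated rates only illustrate it and would change with the assumed missing rate, slope and correlation.

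The effect on the primary results cannot be quantified from the article, which gives no expected missingness. If little is missing, the consequence is small; if losses differ by TSST arm, the equivalence comparison is where bias would matter most. The documents do not support saying that exclusion follows from the test, or that a given share of the 84 participants will be lost to the ANOVA.

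**What to change.** - Remove the MCAR test as a decision rule. It may be reported descriptively.
- For the repeated primary outcomes, make a likelihood-based mixed model on all available observations, or multiple imputation, the default whatever the test shows. The covariance structure can be left to the analysis plan.
- Justify MAR from the recorded reasons for missingness, including VR sickness and distress, and report those reasons by TSST arm.
- Add one simple MNAR sensitivity analysis by TSST arm, for example shifting imputed values by a fixed amount separately in each arm.
- State whether completely missing data means a wholly absent measure or data missing completely at random.

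The cost is a revised section {20c}, a matching adjustment to the model wording in section {20a} if the mixed model is chosen, and slightly more analysis work. R, already named in section {20a}, can do all of it. Design and data collection do not change.

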**Fig. 2 Fig2:**
[figure not shown]
Timeline of Ambulatory Assessment

The second test appointment (T2) will again take place in our facilities and the TSST will be carried out with the participants. Due to the hormonal circadian rhythm and to record greater cortisol responses, all participants will be tested in the afternoon [21]. Furthermore, 8 saliva samples and 9 mood assessments will be taken to capture the psychological and endocrinological stress reactions. Directly after arrival of the participants, the first saliva sample will be taken and the sensor for measuring the heart rate will be attached (about 20 min after arrival). The participants can come to rest by filling out questionnaires and using relaxation material. This will be followed by the TSST, whereby VR glasses or eye-tracking glasses will be first put on, calibrated, and tested before the preparation period of the TSST (5 min) starts. Then, the participants will be confronted with a speech (“Why are you suited for the position of student representative?”) and an arithmetic task (e.g., for 11-year-old participants: “Please count backwards from the number 785 in steps of 7.”) in front of a panel and a camera. Both tasks will be adapted to the age of the participants and last 5 min each. In the TSST-IV, the panel will consist of one female and one male staff member of the department, who have been specially trained to keep gestures, facial expressions, and feedback neutral. Based on the real version, we will use one male and one female virtual human in the TSST-VR. We designed the virtual humans using the computer graphics software Daz3D [22]. We used the characters Genesis 8 Male and Genesis 8 Female [23] and adapted their appearance (body shape, facial expressions, skin, lip synchronization) by morph targets and textures to match the skin type and basic appearance to the real panel members in the TSST-IV. The virtual humans can give visual (taking notes) and auditory (e.g., “Error, please start again.”) feedback that can be triggered by the experimenter via keyboard. These feedback options are similar to the reactions of the panel in the real version. We implemented the VR application using the Unity3D game engine (v. 2019.3.11f1) and modelled a virtual replica of the real environment with identical room dimensions (width: 5.82 m, length: 5.85 m) using the computer graphics software Blender [24] (Fig. 3). We included 3D models of all objects placed in the real environment to ensure the virtual space consists of the same accessory with the same number of potential distractors. To register fixations of the gaze behavior, we defined five 3D Areas of Interest (AOI) using invisible bounding boxes around the male and female virtual human’s face and body, and the camera. We used the maximum bounding box of each AOI to define the *x*, *y*, and *z* dimensions [25]. To immerse the participants in the virtual environment, they will be fitted with an HTC Vive Pro Eye Head Mounted Display (HMD). The HMD has a wide horizontal field of view of 110° and a spatial resolution of 1440 × 1600 pixels per eye. All audio files will be presented via the HMD’s headphones. Participants in VR will perceive the surrounding environment from first-person perspective. The VR application will run on a Dell G5 15 notebook PC (Windows 10, Intel i7-8750H, 8GB RAM, NVIDIA GeForce RTX 2060 Mobile graphics card).

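### The repeated primary variables are assigned to complete-series tests, while the missing-data section offers a likelihood method with no model to run in and makes imputation optional

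*Protocol article*

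**What the plan says.** All references are to the protocol article.

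- **Statistical methods {20a}.** Group and time differences in cortisol, alpha-amylase, heart rate, gaze and mood are examined "by means of (repeated measures) analyses of variance ((rm)ANOVAs, parametric"), or with Mann-Whitney U and Friedman tests if the data are not normal, followed by post hoc t-tests. The factors are "between-subject factors: TSST-VR vs. TSST-IV, HCE vs. NR", with time as the repeated factor. Equivalence tests compare the two TSST conditions, and AUCs summarise the hormone responses. No mixed model or other likelihood-based model is named.
- **Missing data {20c}.** For values missing at random, with contaminated saliva as the example, "multiple imputation and maximum likelihood estimation can be used". The section adds: "Completely missing data (e.g., due to failure of technical components) will be excluded". Outliers may also be excluded. It does not say whether an exclusion removes one value, the child's series or the child.
- **Intervention description {11a}**, text after Fig. 2. At the second appointment "8 saliva samples and 9 mood assessments will be taken".
- **Sample size {14}.** "an effect size of *f* = .30 was expected", and "a sample size of 84 persons was determined to achieve a power of 95" per cent. No allowance for lost samples is given.
- **Interim analyses {21b}.** The study ends when 84 children have been completely tested.

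**The concern.** Classical repeated-measures ANOVA and the Friedman test use only rows with every time point present. An AUC over fixed sampling times also needs each sample, unless a rule for gaps is given. Maximum likelihood on incomplete series needs a model for the series, such as a linear mixed model. Section {20a} names none, so that half of the remedy in {20c} has no analysis to attach to. The other half, multiple imputation, is only permitted.

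If the option is not taken up, the software default is to delete the incomplete series. One contaminated tube or one excluded outlier then removes the child's other seven valid saliva values from that variable's analysis. The set of children would differ between primary variables and would be smaller than the 84 on which the stated power rests. Stopping at 84 tested children is only partial protection: saliva is assayed later at an external laboratory, so contamination may come to light when replacement is no longer possible.

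**Working it through.** **Inputs.** From the protocol: f = 0.30, N = 84, power 95% (Sample size {14}); "The statistical significance level will be set to *α* = .05" ({20a}); 8 saliva samples and 9 mood ratings ({11a}). Assumed, because not stated: two groups compared, m = 8 measures in the power calculation, correlation r = 0.5 between measures, and an independent loss probability p per sample.

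**1. The plan's own figure.** For the between-group effect in a repeated-measures ANOVA, λ = f²·N·m / (1 + (m − 1)r), with 1 and N − 2 degrees of freedom.

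λ = 0.09 × 84 × 8 / (1 + 7 × 0.5) = 60.48 / 4.5 = 13.44, giving power 0.952. N = 84 is therefore reproduced. This is not the only route: four groups with m = 6 and r = 0.3 also give 84. The test behind the plan's figure is thus inferred.

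**2. Children left if only complete series are used.** Share complete = (1 − p)^8; children = 84 × share; power from step 1 with the reduced N.

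| Assumed loss per sample | Share complete | Children | λ | Power, level test |
|---|---|---|---|---|
| 0% | 1.000 | 84 | 13.44 | 0.952 |
| 1% | 0.923 | 77.5 | 12.40 | 0.935 |
| 2% | 0.851 | 71.5 | 11.43 | 0.915 |
| 3% | 0.784 | 65.8 | 10.53 | 0.892 |
| 5% | 0.663 | 55.7 | 8.92 | 0.835 |
| 10% | 0.430 | 36.2 | 5.79 | 0.647 |

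For 9 mood ratings at 5% loss: 0.95^9 = 0.630, or 52.9 children; with m = 9 the power is 0.819.

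**3. The group-by-time test.** Here λ = f²·N·m / (1 − r). At N = 84 this is 60.48 / 0.5 = 120.96; at 55.7 children it is 0.09 × 55.7 × 8 / 0.5 = 80.2. Power stays above 0.999 in both cases, with two groups or four. On these inputs the interaction needs only 18 children (two groups) or 28 (four groups).

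**4. What an incomplete-data method recovers.**

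- *Multiple imputation.* Simulation of the AUC comparison: 800 trials, 3% loss, r = 0.5, difference 0.6 SD (f = 0.30 for two equal groups). Power was 0.964 with full data, 0.900 with complete series only and 0.964 with imputation and pooling. Type I error was 0.036 with imputation and 0.035 with full data.
- *Mixed model.* Approximated by putting m(1 − p) samples per child into step 1 with N = 84. At 5% loss m becomes 7.6 and λ = 0.09 × 84 × 7.6 / (1 + 6.6 × 0.5) = 57.46 / 4.3 = 13.36, giving power 0.951. The 2% and 3% cases also give 0.951.

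**The case against.** The strongest reply is that the plan already contains a workable remedy. Imputation completes each series before the ANOVA, Friedman test or AUC is run. Each group factor has two levels, so its main effect, an AUC difference and an equivalence interval are single contrasts that Rubin's rules pool directly. Pooling rules also exist for tests with several degrees of freedom. Section {20c} gives contaminated saliva as its own example. This stands. A reader might infer that sections {20a} and {20c} cannot be carried out together, or that the plan prescribes complete-case deletion. The documents support neither: deletion is what these tests do by default if the option is not used.

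The sentence on completely missing data most naturally means a wholly absent recording, which no model recovers. That also stands. What remains is that neither this sentence nor the one on outliers limits the exclusion to the affected value.

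The primary outcome is worded as a comparison of changes, which points to group by time, and step 3 shows that this test barely suffers. That limits the size of the point to the level comparison and the AUC.

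A reader might also infer that the groups become unbalanced or that the contrasts are biased. Neither is shown. No loss rate is given, and loss unrelated to group does not unbalance the groups systematically. Adverse event reporting {22} does allow data to be excluded after VR sickness, which could affect one condition more, but nothing indicates how often.

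Finally, covariance structure and pooling details commonly belong in an analysis plan that is not shown. That is fair for the details. It does not cover the choice of method, which {20a} does fix, and fixes without a likelihood model.

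**Conclusion.** The point holds as a mismatch between two sections and a missing commitment. The named repeated-measures methods need complete series, the likelihood option has no model, and the imputation option is discretionary. If the option is left unused, about 71, 66 or 56 of 84 children remain at an assumed 2%, 3% or 5% loss per saliva sample, and power for the between-group level test falls from 95% to about 92%, 89% or 83%. At 1% loss the effect is small (about 94%). These figures rest on assumed, independent losses and on an inferred number of groups, number of measures and correlation. They do not apply to the group-by-time test, nor to Mann-Whitney or t-tests at a single time point. This is an inexpensive improvement worth making, not a defect that invalidates the analysis.

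**What to change.** In Statistical methods {20a}, analyse cortisol, alpha-amylase, heart rate and mood with a linear mixed model fitted by REML to all observed samples. Include TSST condition, relaxation exercise, time and their interactions, and name the within-child covariance in advance with a simpler fallback. Take the TSST-VR minus TSST-IV interval for the equivalence test and the HCE minus NR contrast from this model. Alternatively, keep the ANOVA and change the permissive wording in {20c} to a commitment to multiple imputation, with pooled contrasts.

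In either case, compute AUC from the model or within each imputed data set, and state in {20c} that a contaminated, technically lost or excluded value removes only that sample and not the rest of the child's series.

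The cost is a change of wording in two sections. SPSS and R, both already named, fit the model, and no new data are needed. The small downside is that the covariance structure must be fixed in advance.
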